### Statistical Analysis

#### Sample Size

For this study’s power analysis, the effect size is set at 0.8, which is based on a prior study that had large effect sizes on insomnia (0.8) [28]. The SD is set at 1 and the α is set at .05. Therefore, the required sample size is 32 participants, which is anticipated on the basis of clinical experience that 10%-25% of participants will drop out of the study so an additional 8 participants will be enrolled; thus, 40 participants will be enrolled for a total of 20 participants in each group. Intention-to-treat analyses will be used; hence, in the event of a participant dropping out after randomization, the data from their last assessment will be carried forward to the reassessment [48].

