#### Statistical Approach

##### Aim 1: To Assess the Therapeutic Effect of CBT-I in Individuals With a Subacute Concussion on Insomnia Symptoms and Sleep Quality

An independent samples *t* test will be used to determine if there is a significant difference in percent change in the ISI (primary outcome) and PSQI between the CBT-I and the WLC conditions. To assess maintenance for each group, paired *t* tests will be used to determine if there is a significant difference at the following time points: from the reassessment following CBT-I (reassessment 1 for the CBT-I group; reassessment 2 for the WLC group) to the immediate reassessment following the typical activities period (reassessment 2 for the CBT-I initial group; reassessment 3 for the WLC group), and from reassessment following CBT-I to delayed reassessment (reassessment 1 to reassessment 3 for CBT-I group). The percentage of participants who meet the minimal clinically important difference (MCID) will also be reported (7 points for the ISI [36] and 3 points for the PSQI [39]). In the event that the data do not meet the assumptions for parametric *t* tests, nonparametric tests (Mann-Whitney *U* test for independent samples, and Wilcoxon signed rank test for paired samples) will be used.

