##### Aim 3: To Evaluate the Relationship Between Improvement in Sleep Outcomes and Postconcussion Symptoms

Two simple linear regressions will be run to evaluate the relationship between improvement in sleep outcomes and postconcussion symptoms. The first simple linear regression will determine if change in ISI from preintervention to postintervention stages (predictor variable) will predict changes in postconcussion severity (dependent variable). The second simple linear regression will determine if change in the ISI from preintervention to postintervention stages (predictor variable) will predict changes in the number of postconcussion symptoms (dependent variable). If there are significant differences at baseline in age, gender, medication use, number of concussions, and receiving other services between the two groups, the variables will be entered into the model as a covariate, and the 2 models will be rerun.

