### Anticipated Limitations

Potential limitations related to the treatment response are as follows. First, it is unknown how each participant will respond to the CBT-I treatment with their current symptom burden. Enrolling participants who are within at least 4 weeks of their concussion was to obtain individuals who have relatively stable symptoms at the time of enrollment. Second, medication use and dosage may affect the treatment response to the CBT-I intervention. Therefore, information on medication will be collected at baseline and at reassessments to be included in statistical analysis if indicated. Third, participants will potentially be receiving care from other health care providers, which could impact the interpretation of the results. Therefore, information on type of services being received will be collected at baseline and at reassessments to be included in statistical analysis if indicated.

Another potential limitation to this study is attrition. The attrition rate was 20% in one study evaluating CBT-I in adolescents with a concussion [28]. A 20% attrition rate was also observed in a cognitive behavioral intervention study on adults who have had a concussion [58]. To account for attrition, we will overenroll by 20% in this study. To help with retention, study procedures and time commitment will be clearly articulated to potential participants and reinforced during the course of the study. Furthermore, individuals in the WLC will be contacted by telephone in the middle of their 6-week waiting period to remind them of their upcoming CBT-I sessions and to maintain connection and interest.

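### Carrying the last assessment forward is presented as part of intention-to-treat; it can bias the primary contrast in either direction, hide relapse in the maintenance tests and create a false association in Aim 3

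*Protocol article*

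**What the plan says.** The rule stands in the Sample Size section of the protocol article: "the data from their last assessment will be carried forward to the reassessment". It applies to anyone who leaves once randomised, and the linking word (hence) makes carry-forward follow from intention-to-treat. No aim is exempted, and the article names no other missing-data method and no sensitivity analysis.

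The same section expects 10%-25% of participants to drop out. Anticipated Limitations adds: "The attrition rate was 20% in one study evaluating CBT-I in adolescents with a concussion", and the same rate for a second study in adults.

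Three analyses receive the carried values:

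- **Aim 1, primary.** A t test compares percent change in the ISI between CBT-I and waitlist. Aim 2 uses the same approach.
- **Maintenance.** "To assess maintenance for each group", paired t tests compare the post-treatment reassessment with later ones.
- **Aim 3.** A simple regression asks whether "change in ISI from preintervention to postintervention stages (predictor variable) will predict changes in postconcussion severity"; a second does the same for the number of symptoms.

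**The concern.** Intention-to-treat means that participants are analysed in the group to which they were randomised. Carry-forward is a separate assumption: that a person who left has not changed since the last visit. The article adopts it without saying that it is an assumption.

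The design makes its effects concrete. Assessments are at baseline and weeks 6, 12 and 18, so the only ISI score before week 6 is the baseline one. Anyone lost in that period is entered as exactly unchanged. Anyone lost after the post-treatment visit is entered as having held the benefit exactly. A person who left before finishing CBT-I also gets a maintenance difference of 0, without having shown a benefit to maintain. In Aim 3, anyone lost before the post-treatment visit becomes the point (0, 0).

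At stake are the size of the primary effect, the claim that benefit lasts, and the claim that better sleep goes with fewer symptoms. For the last two, carried values can push the result towards the article's own hypotheses.

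**Working it through.** **Inputs from the article.** Effect size: "the effect size is set at 0.8". Scale and alpha: "The SD is set at 1 and the α is set at .05". There are 20 participants per group and 10%-25% dropout, that is 4 to 10 of 40.

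**Not given, so assumed.** Dropout by arm and by visit, change in the waitlist group, and mean changes in SD units. Placing all dropout before the relevant visit is the upper case.

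**The plan's own figure.** The step from 32 to 40 reproduces: 32/(1-0.20) = 40. The 32 itself does not follow from an effect of 0.8 at two-sided 5% and 80% power (25-26 per arm). That is a separate matter and does not bear on this point.

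**1. Primary contrast.** Let mC and mW be the mean improvements in SD units, and dC and dW the dropout proportions before week 6, with dropout unrelated to outcome. The expected contrast after carry-forward is

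(1-dC)·mC - (1-dW)·mW.

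With equal dropout d this is (1-d)(mC - mW), whatever the waitlist change. For a true contrast of 0.80 with no waitlist change (simulated two-sided power, 20 per arm):

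| Dropout by week 6 | Contrast (SD) | Power |
|---|---|---|
| 0% | 0.80 | 69% |
| 10% | 0.72 | 64% |
| 20% | 0.64 | 58% |
| 25% | 0.60 | 54% |

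With 16 completers per arm the power is 59%, so at 20% dropout most of the power loss comes from losing people. What carry-forward adds here is the shift in the estimate.

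With unequal dropout the direction is open. Take mC = 1.2 and mW = 0.4, a true contrast of 0.80:

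- 25% lost on CBT-I, 10% on waitlist: 0.75×1.2 - 0.90×0.4 = 0.54.
- 5% lost on CBT-I, 25% on waitlist: 0.95×1.2 - 0.75×0.4 = 0.84.

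With no treatment effect and both arms improving by 0.8 SD, 25% against 10% dropout gives 0.60 - 0.72 = -0.12 SD, although the simulated error rate stays near 5%.

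**2. Maintenance (20 people, paired test).** If dropout is unrelated to relapse, a true loss of 0.70 SD with 4 carried values shows as 0.80×0.70 = 0.56. Power falls from 85% to 74%, the same as for completers. If the 4 who leave are the relapsers, each 2 SD worse, and the rest are stable, the true mean loss is 4×2/20 = 0.40 SD. It shows as 0.00, and the rejection rate falls from 20% to 5%.

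**3. Aim 3, no true association.** Let x and y be the changes in ISI and PCSS, with within-person SD 1 and means mx and my, and let a proportion d be entered as (0, 0). The induced covariance is d(1-d)·mx·my, and

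r = d(1-d)·mx·my / √{[(1-d) + d(1-d)mx²]·[(1-d) + d(1-d)my²]}.

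For d = 0.20, mx = 1.5 and my = 1.25: 0.16×1.875 = 0.30; the variances are 0.80 + 0.16×2.25 = 1.16 and 0.80 + 0.16×1.5625 = 1.05; r = 0.30/√(1.16×1.05) = 0.27.

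Simulated false-positive rates at nominal 5%, 40 pairs:

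| Mean change, ISI / PCSS (SD) | 0 carried | 4 carried | 8 carried |
|---|---|---|---|
| 0.8 / 0.4 | 5% | 6% | 8% |
| 0.8 / 0.8 | 5% | 7% | 12% |
| 1.5 / 1.0 | 5% | 12% | 31% |
| 1.5 / 1.25 | 5% | 16% | 42% |

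**The case against.** Several objections are fair and limit the point.

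- **The direction is not fixed.** A reader might infer that the rule always shrinks the primary effect. It does so with equal dropout or with more dropout on CBT-I, but the contrast can rise when many more leave the waitlist, and the article gives no split by arm. Nor is there bias from people who truly did not change.
- **Natural recovery is not established.** A reader might assume that untreated symptoms drift. Anticipated Limitations says that enrolment at four weeks or more was meant to secure fairly stable symptoms, and no drift is quantified. Maintenance and Aim 3 do not need drift; change on treatment is enough.
- **Power against completers.** A reader might infer that carry-forward always costs clearly more power than a completer analysis. With no waitlist change the two are nearly equal (58% against 59%); a clear gap needs improvement in the waitlist arm, which the article does not state.
- **The larger figures are upper cases.** The 10%-25% covers the whole study, and not all of it will fall before the visit in question. In the mildest Aim 3 case the rate is only 6-8%.
- **This is a pilot, and Aim 3 is not primary.** With equal dropout the primary test errs towards caution.

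None of this supports the rule as stated. It makes the size conditional. Caution in the primary test does not help maintenance, where a carried zero can favour the hypothesis, or Aim 3, where the error rate rises.

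**Conclusion.** The point holds in conditional form. Carry-forward does not follow from intention-to-treat, and applying it to every aim is a poor choice for this design.

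- **Primary:** if all dropout precedes week 6 and is equal, 0.80 SD becomes 0.72, 0.64 or 0.60 at 10%, 20% or 25%. If it is unequal, bias can go either way.
- **Maintenance:** relapse is hidden to the extent that those who leave are those who relapsed. If they kept improving, the zero understates benefit instead.
- **Aim 3:** a positive association can arise where none exists, because the article expects both scores to improve. False positives are about 6-16% with 4 of 40 pairs carried and 8-42% with 8, for assumed mean changes of 0.8-1.5 SD in ISI and 0.4-1.25 SD in PCSS.

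These are ranges because dropout timing, its split by arm and the SDs are not stated. The case is clearest for Aim 3 and maintenance.

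**What to change.** State intention-to-treat and the handling of missing scores separately.

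- **Aims 1-2 and maintenance:** fit a likelihood-based repeated-measures mixed model to all observed scores of all randomised participants (baseline, weeks 6, 12 and 18; arm by visit). Take the week-6 arm contrast as primary and estimate maintenance from the same model.
- **Aim 3 and the biomarkers:** use observed pre/post pairs or multiple imputation, never carried-forward pairs.
- **Carry-forward:** keep it at most as a labelled sensitivity analysis.

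The cost is revised analysis wording and a different model; no new data are needed. The model would replace the planned percent-change t test, so the change should be recorded before the data are analysed. It relies on a missing-at-random assumption, which sensitivity analyses can probe but not verify. A participant with only a baseline score adds little information under any method.

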#### Statistical Approach

##### Aim 1: To Assess the Therapeutic Effect of CBT-I in Individuals With a Subacute Concussion on Insomnia Symptoms and Sleep Quality

An independent samples *t* test will be used to determine if there is a significant difference in percent change in the ISI (primary outcome) and PSQI between the CBT-I and the WLC conditions. To assess maintenance for each group, paired *t* tests will be used to determine if there is a significant difference at the following time points: from the reassessment following CBT-I (reassessment 1 for the CBT-I group; reassessment 2 for the WLC group) to the immediate reassessment following the typical activities period (reassessment 2 for the CBT-I initial group; reassessment 3 for the WLC group), and from reassessment following CBT-I to delayed reassessment (reassessment 1 to reassessment 3 for CBT-I group). The percentage of participants who meet the minimal clinically important difference (MCID) will also be reported (7 points for the ISI [36] and 3 points for the PSQI [39]). In the event that the data do not meet the assumptions for parametric *t* tests, nonparametric tests (Mann-Whitney *U* test for independent samples, and Wilcoxon signed rank test for paired samples) will be used.

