#### Mood Questionnaires

The BDI [36] assessment will be used to assess the level of depression. The tool consists of 21 items that are scored on a Likert scale of 0-3 with 0=“no change in symptom” and 3=“severe change in symptom.” Scores range from minimal depression (0-13), mild depression (14-19), moderate depression (20-28), and severe depression (>29).

The BDI completed during screening will yield the baseline BDI score. The Beck Anxiety Inventory (BAI) [45] assessment will be used to assess the level of anxiety. The tool consists of 21 items that are scored on a Likert scale of 1-3 with 0=“not at all” and 3=“severely.” Scores range from minimal anxiety (0-7), mild anxiety (8-15), moderate anxiety (16-25), and severe anxiety (>30).

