### Randomization

Following the baseline assessment, participants will be randomized to either the CBT-I initial group (n=20) or the CBT-I WLC group (n=20; Figure 1). A randomization list was developed using SPSS [46]. Participants are not blinded to their group assignment. One researcher (RL) is providing the treatment for this study and is not blinded to group allocation. Questionnaires are sent to participants via REDCap, and participants will be able to answer the questionnaires on their own time and in their own environment. The same researcher (RL) is also performing data analyses for this study.

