##### Aim 2: To Assess the Therapeutic Effect of CBT-I in Individuals With a Subacute Concussion on the Severity and Number of Postconcussion Symptoms, Anxiety, and Depression

An independent samples *t* test will be used to determine if there is a significant difference in percent change for the PCSS, BAI, and BDI between the CBT-I condition and the WLC group. To assess maintenance, paired samples *t* tests will be used to determine if there is a significant difference from the following time points: from the reassessment following CBT-I (reassessment 1 for the CBT-I group; reassessment 2 for the WLC group) to the immediate reassessment following the typical activities period (reassessment 2 for the CBT-I Initial group; reassessment 3 for the WLC group), or from reassessment following CBT-I to delayed reassessment (reassessment 1 to reassessment 3 for the CBT-I group). The percentage of participants who meet the MCID criteria for each outcome will be reported (12 points for the PCSS, 4 points for the total number of symptoms on the PCSS, 4 points on the BAI, and 5 Points on the BDI [40,45,46]). In the event that the data do not meet the assumptions for parametric *t* tests, nonparametric tests (Mann-Whitney *U* test for independent samples and Wilcoxon signed rank test for paired samples) will be used.

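### Unadjusted tests of percent change lose power on every Aim 1 and Aim 2 outcome, and percent change is undefined at a zero baseline for the secondary BAI and BDI

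*Protocol article*

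**What the plan says.** Under Statistical Approach, Aim 1 uses an independent-samples t test for a "significant difference in percent change in the ISI (primary outcome) and PSQI between the CBT-I and the WLC conditions". Aim 2 does the same for a "significant difference in percent change for the PCSS, BAI, and BDI between the CBT-I condition and the WLC group". Both aims carry a fallback that begins "In the event that the data do not meet the assumptions for parametric" and leads to Mann-Whitney for the group comparison. Neither aim puts the baseline score, or any other covariate, into the comparison.

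On the scales:
- Inclusion criteria and Sleep Questionnaires: ISI must be at least 10 at screening, and the screening ISI serves as baseline.
- Mood Questionnaires: the lowest BAI band begins at zero ("Scores range from minimal anxiety (0-7"), and so does the lowest BDI band.
- Exclusion criteria: BDI has an upper limit only. BAI has no limit at all.

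No rule is given for a baseline of zero. Sample Size promises an intention-to-treat analysis.

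**The concern.** Percent change is (follow-up − baseline) / baseline × 100, and two things follow.

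First, dividing by baseline does not remove the baseline's random variation. It builds that variation into the outcome. A model with the baseline score as covariate uses the same data more efficiently, and a trial of 20 per arm has little power to give away.

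Second, where the baseline can be zero, the outcome does not exist. A participant with a zero BAI or BDI has no value to analyse, despite the intention-to-treat promise. Near zero the value is lopsided: a move from 1 to 5 points is +400%, while no improvement can exceed −100%.

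This second problem belongs to the Aim 2 mood scales, not to the primary outcome.

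**Working it through.** **Power available.** Sample Size gives effect 0.8, SD 1, α 0.05 and 32 required participants (16 per arm), with no power or sidedness. Two-sided, normal approximation: power = Φ(0.8·√(n/2) − 1.96).
- n = 16: Φ(2.263 − 1.96) = 62%.
- n = 20: Φ(2.530 − 1.96) = 72%.
- 80% power would need 25 per arm.

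So 32 does not correspond to a conventional two-sided power. That is a separate matter; here it only shows that power is scarce.

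**Simple analytic check.** An unadjusted change in points has variance factor 2(1 − ρ), and a baseline-adjusted model has 1 − ρ². The article gives no ρ, so 0.3, 0.5 and 0.7 are assumed. With 20 per arm, power = Φ(2.530/√factor − 1.96):

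| ρ | Unadjusted change | Baseline-adjusted |
|---|---|---|
| 0.3 | Φ(2.530/√1.40 − 1.96) = 57% | Φ(2.530/√0.91 − 1.96) = 76% |
| 0.5 | Φ(2.530/√1.00 − 1.96) = 72% | Φ(2.530/√0.75 − 1.96) = 83% |
| 0.7 | Φ(2.530/√0.60 − 1.96) = 90% | Φ(2.530/√0.51 − 1.96) = 94% |

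**Simulation of percent change itself.** 20 per arm, two-sided 5%, integer scores, truncated-normal baselines, follow-up clipped to the scale, undefined percentages dropped. Means, SDs and effects are assumptions:
- ISI: mean 17, SD 4, range 10–28, effect 3.2 (3.2/4 = 0.8, the planned standardised effect).
- BAI: mean 12, SD 9, floor 0, effect 5.
- BDI: mean 15, SD 8, range 0–29, effect 5.

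For BAI and BDI the planned analysis is taken as the t test with a switch to Mann-Whitney when a Shapiro-Wilk test rejects normality. That trigger is also an assumption, since the article names none. For ISI, Mann-Whitney and the t test give nearly the same power.

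| Outcome | Percent change, ρ 0.3/0.5/0.7 | Baseline-adjusted | Loss in points |
|---|---|---|---|
| ISI | 58/72/89% | 72/80/92% | 14/8/3 |
| BAI | 33/41/56% | 40/48/64% | 7/7/8 |
| BDI | 39/49/69% | 50/58/75% | 11/9/6 |

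A rerun with another random seed agreed within two points. With no treatment effect, the planned procedure rejected about 5% of the time.

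**Zero baselines.** If a proportion p score 0, the chance of at least one among 40 is 1 − (1 − p)^40:
- p = 1%: 33%.
- p = 5%: 87%.

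The distributions above gave about 55% of trials with a zero BAI and 31% with a zero BDI. Right-skewed (gamma) baselines of similar mean and SD gave about 8–9% and 1%. The documents cannot choose between these.

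**The case against.** The strongest reply is that the plan already contains a remedy. The Mann-Whitney fallback would be used in most simulated BAI and BDI trials, and ranks are not dominated by a few huge percentages. This largely stands. Judged by the t test alone, a reader might infer losses of 22 to 24 points for BAI and 20 to 27 for BDI, but that is not the analysis the plan would usually run. What survives is that a rank test cannot place an undefined value and still ignores the baseline score.

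It is also fair to say that the primary outcome is never undefined, that its loss is small if correlation is high (3 points at 0.7), and that type I error is not affected.

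Several stronger readings are tempting but not supported:
- **MCIDs in points clash with a percent endpoint.** The MCIDs are used only to report how many participants reach them, which needs no percent result.
- **Promised covariates have nowhere to go, or would bias the arm comparison.** Anticipated Limitations says only that medication is "to be included in statistical analysis if indicated". Aim 3 does give medication and services a place ("the variables will be entered into the model as a covariate, and the 2 models will be rerun"). Nothing says that post-randomisation medication will adjust the group comparison.
- **The test is chosen post hoc.** The fallback is written in advance. That the unblinded treating researcher "is also performing data analyses for this study" is a separate issue.
- **The waitlist arm's later CBT-I phase is pooled into the CBT-I side.** The wording is loose, but the hypotheses set CBT-I against the waitlist control, there are two randomised groups and the test is for independent samples.
- **PCSS is equally exposed to zeros.** Its scale starts at 0, but everyone enrolled has sleep difficulty, which the article counts among postconcussion symptoms, so a zero total is implausible.

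**Conclusion.** The point holds in two parts of different reach. For every Aim 1 and Aim 2 comparison, the plan leaves the baseline score unused as a covariate. On the primary ISI this costs about 3 to 14 points of power with 20 per arm, depending on a correlation that the article does not give. For the secondary BAI and BDI the endpoint can also be undefined, and even with the rank fallback about 6 to 11 points are lost under the assumed distributions.

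The direction was the same in every setting tried; the sizes rest on assumed means, SDs, effects, correlations and fallback trigger. The analysis is not shown to be invalid, and the primary outcome is not at risk of undefined values. This is an avoidable weakness worth correcting.

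**What to change.** For each Aim 1 and Aim 2 outcome, compare the two randomised groups at reassessment 1 (week 6) with a linear model of the score on arm and baseline score, and report the adjusted difference in points with a 95% CI. Naming the time point and the randomised groups also removes the loose wording about conditions.

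In place of the switch to Mann-Whitney, use a robust-standard-error or permutation version of the same model as a sensitivity analysis. Keep percent change as description only.

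The cost is one regression per outcome and one degree of freedom. No new data are needed, because baseline and week-6 scores are already collected and a zero baseline becomes an ordinary covariate value. The article describes data collection as still under way, so the change could be made before analysis.

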**Results:**

Enrollment of 40 participants was completed July 2022, data collection will be completed in November 2022, and publication of main findings is anticipated in May 2023. It is anticipated that participants experience reduced insomnia symptoms and postconcussion symptoms following CBT-I and these improvements will be retained for at least 12 weeks. Additionally, we expect to observe a positive correlation between sleep and postconcussion symptom improvement.

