### Objectives and Hypotheses

#### Aim 1: To Assess the Therapeutic Effect of CBT-I in Individuals With a Subacute Concussion and Symptoms of Insomnia on Sleep Outcomes

We hypothesize that CBT-I will result in a greater magnitude of change in insomnia severity and sleep quality compared to the waitlist control (WLC). Furthermore, we hypothesize that the magnitude of change in insomnia severity and sleep quality will be maintained for 12 weeks following CBT-I.

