## Methods

### Study Overview

The proposed study is a delayed-start randomized controlled trial of 6 weeks of CBT-I among individuals with a concussion, aged 18-64 years old (n=40; Figure 1). Individuals who meet the inclusion criteria (Textbox 1) will be randomized into 2 groups. The first is a CBT-I initial group (CBT-I initial; n=20), which will start the CBT-I intervention directly after completing the baseline assessment. The second group is the WLC group (n=20), which will start the CBT-I intervention 6 weeks after the baseline assessment. The final 6 weeks for all participants, regardless of group assignment, will include participation in typical activities such as maintaining employment status, family roles, etc. 

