#### Reassessments

Reassessments will occur 6, 12, and 18 weeks following baseline. Participants will update their current medications and health care services. Additionally, sleep questionnaires, concussion symptoms, and mood questionnaires completed during baseline will be completed at reassessments.

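### The Aim 1 claim that gains are maintained for 12 weeks is tested only for a difference, with no maintenance criterion, so a non-significant result cannot support it

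*Protocol article*

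**What the plan says.** Under Objectives and Hypotheses, Aim 1, the article states: "we hypothesize that the magnitude of change in insomnia severity and sleep quality will be maintained for 12 weeks following CBT-I". The abstract's Results section expects that "these improvements will be retained for at least 12 weeks".

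The Statistical Approach for Aim 1 gives the method for each group separately: paired t "tests will be used to determine if there is a significant difference at the following time points: from the reassessment following CBT-I" to the visit that closes the typical-activities period ("reassessment 2 for the CBT-I initial group; reassessment 3 for the WLC group"), and then, for the longer interval, "from reassessment following CBT-I to delayed reassessment (reassessment 1 to reassessment 3 for CBT-I group". Wilcoxon signed rank tests are the fallback. The section also reports the percentage of participants reaching the MCID (7 points on the ISI, 3 on the PSQI), but does not connect that percentage to maintenance.

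On timing, "Reassessments will occur 6, 12, and 18 weeks following baseline", and the waitlist (WLC) arm is the one "which will start the CBT-I intervention 6 weeks after the baseline assessment". The Sample Size section puts 20 people in each arm, expects 10% to 25% dropout, and handles it by carrying the last assessment forward. The Statistical Approach for Aim 2 repeats the same paired tests to assess maintenance, although the Aim 2 hypothesis says nothing about maintenance.

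**The concern.** Maintenance is a claim that little or nothing is lost. A paired t test takes no change as its null hypothesis, so it can produce evidence of loss but not evidence that loss is absent or small. If the gains are stable, the expected result is non-significance, and a small or incomplete sample gives the same result. With no other criterion stated, a non-significant test is the only available result that a reader would be likely to take as support for stable gains.

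What is at stake is the durability conclusion, which is half of the Aim 1 hypothesis and appears in the abstract. A partial relapse could pass as maintenance. The carry-forward rule pushes in the same direction, because it fills missing later visits with earlier scores.

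**Working it through.** **The plan's own figure.** There is none for this question. The stated sample size is for the between-group comparison, and no power or precision is given for the maintenance tests.

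**Follow-up by arm.** The CBT-I initial arm has its post-treatment visit at week 6 and its last visit at week 18: 18 − 6 = 12 weeks. The WLC arm starts at week 6 and has its post-treatment visit at week 12: 18 − 12 = 6 weeks. The 12-week contrast therefore exists in one arm of 20.

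**Inputs.** n = 20 per arm and α = .05 come from the Sample Size section. Sidedness is not stated; two-sided is assumed. The SD of paired ISI change, σ, is not given; 4 to 7 points is assumed. A loss is a rise in ISI score after the post-CBT-I visit.

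**Chance that a true mean loss δ is non-significant.** The test rejects when |mean change| / (s/√20) exceeds t(.975, 19) = 2.093. Under a true loss δ, the statistic is noncentral t with 19 df and noncentrality √20 × δ/σ. For δ = 3 and σ = 5 this is 4.472 × 0.6 = 2.68, giving 72% power and a 28% miss rate. Across the range:

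| Assumed SD | 95% CI half-width, 2.093σ/√20 | Loss of 2 missed | Loss of 3 missed | Loss of 3.5 missed | Loss of 7 missed |
|---|---|---|---|---|---|
| 4 | 1.87 | 44% | 11% | 4% | <0.1% |
| 5 | 2.34 | 60% | 28% | 16% | <0.1% |
| 6 | 2.81 | 71% | 44% | 30% | 0.1% |
| 7 | 3.28 | 77% | 56% | 44% | 1.1% |

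Without reference to ISI points, a true loss of 0.5 SD of the paired change is missed 44% of the time at n = 20.

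**Effect of carrying forward.** In the initial arm, a person who leaves after reassessment 1 but before reassessment 2 contributes an exact zero to both contrasts. One who leaves before reassessment 1 also contributes zero, with baseline filled in throughout. One who leaves between reassessments 2 and 3 contributes the earlier change to the 12-week contrast. The simulation assumed that 4 of 20 (the 20% attrition cited under Anticipated Limitations) contribute zeros. A true mean loss of 3 then shrinks to 3 × 16/20 = 2.4, and at SD 5 the miss rate rises from 28% to about 39% (at SD 6, from 43% to 54%). Analysing only the 16 observed people gives about the same 39%. The distinctive harm of carrying forward is therefore the shrunken mean, while most of the rise in misses reflects lost information.

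**Is a proper criterion feasible with the enrolled sample?** Suppose maintenance is concluded when the upper 95% limit for mean loss lies below a margin M (one-sided .025), and the true loss is zero. The noncentrality is √20 × M/σ. With M = 3.5, half the ISI MCID and only an example, power at n = 20 is 96%, 84%, 70% and 56% for SD 4, 5, 6 and 7. With M = 3 it is 89%, 72%, 56% and 44%.

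**The case against.** The strongest reply is that the article never says a non-significant test will be read as maintenance. It says only that the tests look for a difference, and a fuller protocol or a statistical analysis plan may hold more. This stands in part: a reader might infer that rule, but it is not written. What remains is that the article names a procedure for this hypothesis, and that procedure cannot show what the hypothesis asserts.

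A reader might also infer that the durability conclusion is unsupported whatever the tests show. That goes too far. A significant loss would be valid evidence against maintenance, and a significant further gain would support it. Only the non-significant result is uninterpretable.

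Nor would the test miss a total relapse: a mean loss of 7 points would almost surely be detected under every SD tried.

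The single-arm 12-week contrast might look like a hidden flaw. It is disclosed in the Aim 1 analysis and follows from the delayed-start design. The initial arm is a randomised half of the sample and can address 12 weeks, with less precision. The fault is only that the hypothesis and abstract state 12 weeks without that qualification.

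Finally, maintenance is secondary in a study the abstract calls a pilot, and the primary ISI comparison does not depend on it. That stands and limits the severity.

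**Conclusion.** The concern holds in limited form. The maintenance hypothesis is paired with a test of difference and no criterion, so the result most likely under stable gains cannot support the hypothesis. The weakness is for partial relapse, roughly 2 to 3.5 ISI points. At n = 20 a true 3-point loss goes undetected 11% to 56% of the time, and carrying forward adds to this.

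The sizes rest on an assumed SD of paired change of 4 to 7 points, two-sided testing at .05, normal changes and, for the carry-forward figure, four zeros among 20. The logical point needs none of these assumptions. This should be fixed, but it does not threaten the primary analysis.

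**What to change.** - For ISI and PSQI, report the mean change from the post-CBT-I visit with a 95% CI. Conclude maintenance only if the limit for loss lies within a margin fixed before the data are examined and justified against the plan's own MCIDs. Otherwise call the result inconclusive. Half the MCID is one example; the choice belongs to the investigators. Fixing it in advance matters because one unblinded researcher both delivers treatment and analyses the data.
- Do not count carried-forward zeros as evidence of maintenance. Base the estimate on observed follow-up, or on a missing-data method that does not assume no change.
- In the Aim 1 hypothesis and the abstract, state that the 12-week result comes from the CBT-I initial arm only and that the WLC arm supports 6 weeks.
- Optionally, add a combined-arm estimate at 6 weeks after treatment, adjusted for arm. At SD 5 and n = 40 its CI half-width is about 1.6 points, against 2.3 in one arm.
- For Aim 2, which states no maintenance hypothesis, report the same changes with CIs and do not infer maintenance from non-significance.

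The cost is wording and a stated margin, with no new data. Enrolment is complete, so the margin must be justified against a fixed sample. The downside is that some truly stable outcomes would be reported as inconclusive: with a 3.5-point margin and all 20 observed, 100% − 84% = 16% at SD 5 and 100% − 56% = 44% at SD 7.
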